### Ethical issues

The study protocol has been approved by the Ethical Committee of the University Hospital of Ghent (B670201526906) prior to the beginning of the recruitment. Additionally, approval was obtained from the local Ethical Committees affiliated to the participating memory clinics. Written informed consent will be obtained from all patients before initiation. The study is registered at ClinicalTrials.gov: NCT02630446.

## Discussion

A first major strength of this trial is its contribution to the need for evidence on effectiveness and cost-effectiveness of in-home respite care. To date no other studies measured effectiveness and cost-effectiveness of an in-home respite service similar to the Baluchon service. Findings of this trial can also contribute to the elaboration of future directions of healthcare policies. After all, if in-home respite is effective in supporting informal caregivers and also cost-effective, policy makers should consider reimbursement of in-home respite care.

This trial has several methodological strengths often lacking in previous research. First of all, this study only uses international, validated, and widely used measurement tools to measure the research outcomes. Also, to better adapt some instruments to the Belgian context and this trial, adjustments were made for some instruments. When no valid translation in Dutch of French for Belgium was present we used a proper forward-back translation technique. Secondly, we performed a sample size calculation to know the necessary amount of caregivers needed to show an effect in the primary outcome given a certain effect size. In this analysis we also took into account an average drop-out rate to be expected. Additionally, intention-to-treat will be used to take into account drop-outs. To avoid bias and confounding, often occurring in non-randomized controlled trials, we will use propensity-score matching to simulate an RCT setting. In this way, the found intervention effects can be considered unbiased estimates of the real effect. Finally, active components of the intervention are clearly described, reasons for drop-out will be documented and characteristics of drop-out participants will be compared to those who completed the trial.

Despite the promising contribution of this study to community-based dementia care, several limitations need to be mentioned as well. First, there is a threat towards internal validity because the used quasi-experimental study design lacks random assignment of study groups. Although we use inclusion criteria to increase comparability and statistical efforts such as propensity score matching will be untaken, there can still be unmeasured confounders influencing causal inference. Nevertheless, for this particular research, a quasi-experimental design was preferable over a randomized controlled trial for feasibility and ethical reasons. First of all, the limited capacity of Baluchon Alzheimer Belgium makes it impossible to set up a RCT. Also, it can be seen as ethically unacceptable to randomly assign dyads to one of the trials arms. In this way some caregivers get free respite care while others cannot have this support during the trial.

Second, we only recruited caregivers asking for in-home respite care themselves in the intervention group and caregivers prepared to utilize this service in the control group. Therefore we cannot speculate whether effects might be different for caregivers not asking for or considering this type of support. Also, there is a high probability that caregiver/care-recipient dyads in the intervention group with lower socioeconomic status and lower educational level will be underrepresented because Baluchonnage is normally a rather expensive service that is not commonly known in Belgium. Nevertheless, we will use statistical techniques, such as propensity score matching, to respond to this problem. Also, the fact that participants receive the in-home respite care five days for free can also reduce the gap in socioeconomic status between intervention en control group.

Another important limitation of this trial is a consequence of not controlling the exact duration of the received in-home respite care period in the intervention group. The latter would not be acceptable due to ethical considerations and limited capacity of Baluchon Alzheimer Belgium. Even by setting a minimum duration of five days as an inclusion criterion, differences in outcome variables can still be caused by differences in duration. Nevertheless, to minimalize this phenomenon subgroup analyses can be undertaken. The same applies for intervention dyads who already received in-home respite in the past. After all, we can expect that dyads who are already familiar with in-home respite care react differently from people who are about to utilize it the first time. It is known that trust plays a crucial role in accepting respite care [44, 45]. Finally, use of other supportive strategies such as day care or night-time care can also influence results for which subgroup analyses can be undertaken if necessary.

Like other supportive interventions for caregivers this study only has a rather limited duration and a short follow up period. A longer time period could produce different outcomes or show certain effects to be strengthened, weakened, or sustained over time. Because dementia is a slow degenerative process, it can be expected that differences in time to nursing home placement between the study groups will not be found on such short notice. Therefore, to allow conclusions about possible difference in time to placement, we will measure intention to institutionalize which is seen as an adequate predictor for real placement into a nursing home [46]. Also, we will obtain the National Registration Number of dementia participants allowing to trace information on resource use and time to nursing home placement over a longer time period than the trial. Finally, we will perform modeled-based cost-effectiveness analyses to extrapolate results over a longer period.

Due to time constraints, organizational limitations, and high geographical distribution of study participants, assessments after the first baseline assessment will be done by telephone interviewing. Although no evidence was found indicating that the used instruments are not suited for telephone interviewing and data collection by telephone is widely performed and well accepted, face-to-face interviewing still remains the most preferred type of collecting data.

To measure differences in quality of life of caregivers, QALYs will be obtained from the EQ-5D. It is known that this generic preference-based measure of health lacks sensitivity in determining differences especially in emotional and mental health problems, and even more in short periods. Because it is to be expected from this intervention that in particular those emotional and mental health dimensions will shift, the question can be asked if the EQ-5D will be sensitive enough to show an effect on such short notice. Still, its use is preferred over the use of other disease-specific instruments, which have proven to be more sensitive, because the developed algorithms to translate the obtained scores into health utilities have been subject to a lot of criticism in literature.

Despite the described limitations, inherent to the complex nature of investigating respite care services, this study will have great added value because to date no studies measured effectiveness and cost-effectiveness of an in-home respite service similar to the Baluchon service. Results of this trial can give much more insight in potential benefits and disadvantages of community-based respite care, especially for informal caregivers and the healthcare system, but also for care-recipients. Conclusions based on this trial can thus help policy-makers in considering future directions of dementia care.

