### Statistical analysis

First of all, descriptive statistics will be represented to draw a clear profile of the characteristics of study participants. Therefore the mean, percentages, and the standard deviations of quantitative variables will be displayed. To determine possible baseline differences between the groups, mean values of baseline characteristics will be compared using independent sample t-tests for continuous variables if normally distributed or by performing Pearson’s chi-square test for categorical variables. To help control for bias and confounding, statistical techniques such as propensity score matching will be used. Propensity score matching can be seen as a tool to simulate a RCT setting. In this way we can expect the observed effect to be an unbiased estimate of the real effect [41, 42].

To investigate possible effects of the intervention on the primary and secondary outcomes, analysis of variance will be conducted if the outcome variables are normally distributed. A *P*-value of 0.05 will be considered as significant. All analyses will be based on intention to treat also taking drop-outs into account and avoiding overestimation of respite care effects.

When the intervention is effective a cost-effectiveness analysis in a separate economic evaluation plan will be performed. ICERs will be calculated for the mean and upper and lower confidence levels of the costs and consequences. To explore uncertainty one-way-sensitivity analysis will be conducted around the ICER and illustrated in a Tornado diagram. Additionally, on all input variables a probabilistic sensitivity analysis, also called Monte Carlo analysis, will be conducted to test robustness of the model. These results will also be illustrated. Finally, the results and the willingness to pay threshold of the Belgian Health Care System will be presented in a cost-effectiveness acceptability curve [34].

To compare time to nursing home placement of persons who use respite care to those who do not, we will use Kaplan-Meier survival curves to illustrate association between the comparison groups. By additionally conducting a log-rank test statistical difference between the groups in time to placement can be found [43].

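### The article says propensity score matching makes the effect estimate unbiased, which contradicts its own limitation on unmeasured confounders, and the only comparability check it states can miss relevant imbalance

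*Protocol article*

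**What the plan says.** Two places describe what matching will achieve. The Statistical analysis section presents propensity score matching as a way of imitating a randomised trial and adds: "In this way we can expect the observed effect to be an unbiased estimate of the real effect". The Discussion lists the same step as a methodological strength ("we will use propensity-score matching to simulate an RCT setting") and concludes: "In this way, the found intervention effects can be considered unbiased estimates of the real effect".

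The limitations part of the Discussion takes the opposite position. After naming the inclusion criteria and the matching, it says "there can still be unmeasured confounders influencing causal inference".

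On comparability, the Statistical analysis section gives one procedure. Its purpose is stated as "To determine possible baseline differences between the groups", and the method is that "mean values of baseline characteristics will be compared using independent sample t-tests for continuous variables if normally distributed", with a "chi-square test for categorical variables". No other check of group comparability is described.

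**The concern.** Matching on a propensity score can balance only the covariates that enter the score. The resulting estimate is unbiased only if no confounder is left out, the groups overlap, and balance is actually reached. The two sentences state the result without these conditions, in a design where the route into each group is itself related to need and to help-seeking.

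The comparability check has a separate weakness. A p-value mixes the size of an imbalance with the sample size, so a non-significant test does not show that the groups are alike.

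The stake is how the result is read. The Cost-effectiveness analysis section makes the economic evaluation depend on an effect being shown, and the Discussion links effectiveness and cost-effectiveness to reimbursement. A confounded difference described as unbiased would carry that description into both.

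**Working it through.** **1. The statements side by side.** Statistical analysis: matching leads to an unbiased estimate, with no condition. Discussion, strengths: the same. Discussion, limitations: confounders may remain after matching. The first two cannot hold as written if the third does.

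**2. Which statement fits the design.**
- Recruitment: intervention dyads enter when they ask Baluchon for respite. Controls enter through general practitioners, memory clinics, expert centres and a sickness fund, and need only express interest.
- Study participants: controls must never have used Baluchon, while intervention dyads may have. No control can match a prior user on this variable. The Discussion itself expects prior users to react differently.
- Tables 1 and 2: reason for respite is recorded at T0 in the intervention group and at T2 in the control group, so it is not a common baseline covariate.
- Background characteristics: income is not listed, although the Discussion calls the service rather expensive.

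The limitation therefore describes this trial, and the unconditional sentences do not.

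**3. The plan's own sample size.** Inputs from Sample size: difference 6 ZBI points, SD 15 (d = 6/15 = 0.4), alpha 0.05 (two-sided assumed), power 80%, dropout 20%.

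n per group = 2 × (1.960 + 0.842)² / 0.4² = 98.1, rounded up to 99. Then 99 / 0.8 = 123.75, rounded up to 124, and 2 × 124 = 248. Both stated figures are reproduced.

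**4. Sensitivity of the baseline t-test.** The 0.05 level is taken from the general P-value statement. The standardised imbalance (SMD) is an assumption, shown as a range.

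SE of the SMD = √(1/n₁ + 1/n₂); noncentrality = SMD / SE.
- 124 vs 248: SE = 0.110. At SMD 0.20 the noncentrality is 1.82 and power is 44%, so 56% are missed.
- 124 vs 124 (assumed 1:1 match, test repeated): SE = 0.127. At SMD 0.20 the noncentrality is 1.57 and power is 35%, so 65% are missed.

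| True SMD | Power, 124 vs 248 | Power, 124 vs 124 |
|---|---|---|
| 0.10 | 15% | 12% |
| 0.20 | 44% | 35% |
| 0.25 | 62% | 50% |
| 0.30 | 78% | 65% |
| 0.40 | 95% | 88% |

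The smallest observed SMD that reaches p < 0.05 is t(0.975) × SE, which is 0.216 at 124 vs 248 and 0.250 at 124 vs 124. For a categorical variable at an assumed 50% vs 40%, power is 45% and 35%.

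**5. What an uncorrected imbalance could do.** For a confounder whose correlation with burden is assumed to be 0.3 to 0.7, bias = correlation × SMD × SD. At SMD 0.20 this is 0.3 × 0.20 × 15 = 0.9 points to 0.7 × 0.20 × 15 = 2.1 points, or 15% to 35% of the planned 6.

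If the true effect were zero and 99 vs 198 dyads completed, SE = 15 × √(1/99 + 1/198) = 1.85. A bias of 1 point would raise the false-positive rate from 5% to about 8%, and a bias of 2 points to about 19%.

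**6. What an E-value would show (illustration).** Assume 99 vs 99 matched completers and an observed difference of exactly 6. SE = 15 × √(2/99) = 2.13, and the lower 95% limit is 6 − 1.96 × 2.13 = 1.82 (d = 0.121).

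With RR = exp(0.91d), the values are 1.44 and 1.117. With E = RR + √(RR × (RR − 1)), the E-values are 2.23 for the estimate and 1.48 for the limit. An unmeasured confounder associated with both group and outcome by risk ratios of about 1.5 could bring the lower limit to zero.

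**The case against.** The strongest reply is that the article already carries the caveat. Lack of randomisation and unmeasured confounding form its first stated limitation, and the quoted strengths sentence is discussion text, not a decision rule. This stands in part. A reader might infer that the plan binds the authors to report a confounded difference as the real effect, but nothing in it requires a result to be reported without the caveat. The contradiction remains, and one side of it sits in the Statistical analysis section.

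A second reply concerns the significance tests. They are described before matching is mentioned, within the descriptive profile, and are never called the diagnostic after matching. Matching will be used whatever they show. This also stands, so the figure for 124 vs 124 applies only if the tests are repeated. Nor do the tests always fail: a gap of 0.4 SD is found with 95% power at 124 vs 248. That standardised differences, calipers or covariate lists are not given is no finding, because an analysis plan may hold them.

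Three stronger readings are tempting and not supported.
- **That caregiver strain is unmeasured.** Burden, reactions to behaviour, desire to institutionalise, waiting-list status, caregiving time and resource use are all recorded at T0 in both groups. Education and employment are partial proxies for socioeconomic status.
- **That a baseline ZBI gap illustrates unmeasured confounding.** ZBI is measured at baseline in both groups and can enter the score.
- **That the article wrongly expects matching to restore under-represented low-status dyads.** The sentence that follows concerns the gap between the two groups, which matching on measured education can address. The direction of matching is not stated.

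**Conclusion.** The point holds as a contradiction with a supporting weakness. Two sentences claim an unbiased estimate without condition, and the same article says unmeasured confounders may remain. Differing recruitment routes, prior use in one group only, reason for respite recorded at different times and no listed income make the unconditional claim untenable here.

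The stated baseline tests can miss relevant imbalance: 56% of the time for a true 0.2 SD difference at 124 vs 248, and 65% at 124 vs 124 under an assumed 1:1 match with the tests repeated. These rates rest on a two-sided 0.05 level. The bias and E-value figures are illustrations under the assumptions given with them and do not estimate the bias in this trial. The sample size is unaffected.

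**What to change.** In the Statistical analysis section and in the strengths part of the Discussion, replace the two sentences with one statement: the estimate is adjusted for measured confounders only, and is unbiased only if there is no unmeasured confounding and if balance and overlap are achieved. This brings both places into line with the limitations text.

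Judge group comparability before and after matching by standardised mean differences instead of p-values. Report a sensitivity analysis for unmeasured confounding, such as an E-value, beside the 6-month ZBI result.

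The cost is a text change, a little more analysis and a more cautious conclusion. No additional dyads or assessments are needed.

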## Abbreviations

ADL: Activities of daily living
CVM: Contingent valuation method
DTI: Desire to institutionalize scale
EQ-5D: EuroQol 5 dimensions
GDS: Global deterioration scale
ICER: Incremental cost-effectiveness ratio
KCE: Belgian health care knowledge centre
QALY: Quality adjusted life years
RCT: Randomized controlled trial
RIZIV/INAMI: National Institute for Health and Disability Insurance
RMBPC: Revised memory and behavioral problems checklist
RUD: Resource use in dementia
SD: Standard deviation
ZBI: Zarit burden interview
